#### Sample Size

Sample size was estimated based on information from a previous study [18] enrolling patients with MCS allocated to advanced robotic verticalization using the Erigo^®^ (Hocoma, Volketswil, Switzerland) device or traditional verticalization with a traditional tilt table. The comparison of the LCF score between the two groups after eight weeks of treatment led to an increase from 3.13 ± 1.41 to 3.60 ± 1.50 in the control group (n = 15) and from 3.60 ± 1.05 to 4.40 ± 1.06 in the experimental group (n = 15; effect size f = 0.248). For a two-sided α of 0.05 and a power of 80%, we will estimate enrolling at least 49 subjects per arm (VEM and TV). To account for a possible dropout rate of 20%, a total of 118 patients will be enrolled (59 subjects per arm).

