### 2.6. Statistical Plan

All analyses will be conducted by blinded statisticians. Frequencies (percentages) or mean ± standard deviation will be used for descriptive statistics regarding socio-demographic and clinical variables, as well as for the level of satisfaction with the experimental intervention and the occurrence of side effects.

Given that most outcomes are ordinal or exhibit skewed distributions, we will employ linear or generalized linear mixed-effects models (LMM/GLMM) with appropriate link functions. Ordinal outcomes will be analyzed using cumulative logit mixed-effects models, with random intercepts for patients and for enrolling centers. Continuous outcomes approximately normally distributed will be analyzed with LMM, while skewed continuous outcomes will be modeled with appropriate link functions (e.g., log). All models will adjust for baseline values of the outcome (ANCOVA framework) and include time (T0, T1, T2) and group (VEM, TV) as fixed effects, plus their interaction. Model formulas were defined a priori. The following is an example:logit[P(Y_ij_ ≤ k)] = β_0_ + β_1_Group_i_ + β_2_Time_j_ + β_3_Baseline_i_ + β_4_(Group_i_ × Time_j_) + u_patient(i)_ + u_center(i)_
where u_patient(i)_ and u_center(i)_ are random intercepts for patient and center, respectively.

All analyses will be performed with a two-sided significance level of 0.05. Adjustment for multiple comparisons will be made using Benjamini–Hochberg false discovery rate correction. Statistical analyses will be conducted using R (version 4.4.3; R Foundation for Statistical Computing, Vienna, Austria) or equivalent statistical software. Interim analyses are planned at half of the expected sample for safety outcomes only (i.e., AEs).

Patients violating the VEM-sABI protocol will be excluded from the VEM or TV treatment, but the last clinical observation will be considered for statistical analysis, according to an intention-to-treat approach and a Missing at Random (MAR) assumption inherent to the mixed-model framework. To explore the robustness of the results in scenarios where data may be Missing Not At Random (MNAR), we will conduct pre-specified sensitivity analyses using multiple imputation and, where appropriate, alternative approaches such as joint modeling or delta-adjusted pattern-mixture models.

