Protocol violations include: ex-novo administration or change in dose of proscribed drugs (see list in Appendix B), occurrence of severe AE, transfer to acute wards due to severe medical complications, futility of the intervention (as the patient regains the ability to maintain a 90° upright position for ≥15 min without signs of hemodynamic instability on two consecutive days, combined with functional trunk and lower limb control as reflected by a score of ≥3 in the mBI sub-items “Ambulation”, i.e., constant presence of one or more assistants is required during ambulation, and ≥5 in the sub-item “Stair climbing”, i.e., the patient is able to ascend/descend but is unable to carry walking aids and needs supervision and assistance), missing two consecutive sessions or more than five total sessions or request from patients or their legal representative to withdraw from the study.

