## 3. Discussion

Patients with sABI are characterized by high clinical complexity, severe cognitive motor disabilities, and an increased risk of developing clinical complications [42,43,44]. An appropriate and skilled comprehensive rehabilitation intervention can significantly impact clinical outcomes and improve the quality of life of patients and their caregivers [1,2,45,46,47]. An early verticalization can promote patients’ recovery and prevent cognitive-motor disabilities and clinical sequelae [3,4,5]. The present multicenter VEM-sABI study will provide new insights into the still-debated efficacy and usability of a device considered safer for verticalization of patients with sABI because it combines robotic verticalization with lower limb mobilization [12]. The study aims to achieve several outcomes. Firstly, it is expected to enroll a large and homogeneous cohort of patients with sABI admitted to post-acute rehabilitation settings. This goal could minimize the methodological bias of the available literature on this field, which most often involved small and heterogeneous patient cohorts (e.g., chronic patients with sequelae of sABI) [5,8,12,13,14]. In addition, we planned to specifically address this topic in post-acute rehabilitation, where the likelihood of patient clinical improvements due to neuroplasticity [18] and the occurrence of clinical complications are higher [42,43,44]. Moreover, we expect that the two cohorts of patients allocated in the experimental and control arm will not differ in terms of demographic and anamnestic characteristics, to avoid biases in evaluating efficacy and usability of the two treatments. Conversely, differences in clinical characteristics and cognitive functions between patients with pDoC and those eDoC are expected. For this reason, targeted clinical and neurophysiological measures will be adopted to detect specific changes in outcome as a function of clinical diagnosis and to identify patients’ profiles with high probability to respond to both (or at least one of the two) treatments. Additionally, we expect the following study outcomes from the data analysis: (i) an improvement of cognitive levels, disability, and motor function at the end of the treatment in both arms, with a significant recovery in the VEM group, in accordance with previous studies [14]; (ii) a more consistent improvement of lower limb strength, and higher reduction in spasticity in the VEM group because of combined controlled mobilization in the VEM device; (iii) lower occurrence of side effects (e.g., orthostatic hypotension) and related dropouts in the VEM arm; (iv) higher occurrence of discontinuation of verticalization due to “treatment futility” in the eDoC patients, as they are more susceptible to early regain vertical posture and gait. A further analysis of motivations of dropouts will identify clinical profiles of patients who could better match the robotic (VEM) or the traditional tilt table treatment (TV); (v) a reduction in clinical complications occurrence in both groups, based on the potential impact of verticalization on patients overall clinical stabilization [3,4]. Because most participating centers are not familiar with this robotic technology in rehabilitation of patients with sABI, we expect to see higher therapist’s compliance for traditional tilt table (i.e., higher SUS score), especially in the early stages of the study. A preliminary structured 3-day training provided by the robotic device manufacturer, on the appropriate use of the robotic device, including real-life testing on at least two different patients, will be performed to avoid potential challenges and ensure the homogeneity in the device use. To ensure ongoing protocol fidelity and inter-site consistency, we implemented the following measures: (i) competency checklist for certification to assess each operator’s ability to manage setup, tilt procedures, stepping control, safety monitoring, and patient interaction; (ii) monitoring parameters (stepping frequency, tilt parameters, adverse events). Ongoing technical and clinical support, throughout constant availability via phone calls and monthly video-call meetings, will be further provided by the coordinator to address possible concerns. We also forecast to identify changes in neurophysiological indices (as measured by EEG) and blood-biomarkers of brain plasticity in patients who will present clinical improvements. In addition, we hope that neurophysiology and biomarkers can detect any sub-clinical (para-clinical) changes caused by the two verticalization procedures. Thus, the two outcome measures will be able to provide useful information to identify patients with a high probability of response to verticalization and help clinicians plan the most appropriate and personalized treatment in such a specific population of patients with sABI.

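### A mixed model does not secure MAR: given only arm and baseline LCF it is doubtful here, and arm-differential removal could bias the VEM–TV contrast if T1 LCF is then missing

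*Protocol article*

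**What the plan says.** All references are to the protocol article.

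- **Model (section 2.6).** LCF is ordinal, so it falls under the cumulative logit mixed model. The fixed effects are group, time, baseline value and group by time. The random intercepts are for patient and centre. The formula is labelled an example.
- **Missing data (section 2.6).** Patients who violate the protocol stop the assigned treatment. Their latest clinical rating enters the analysis "according to an intention-to-treat approach and a Missing at Random (MAR) assumption inherent to the mixed-model framework". Multiple imputation, joint modelling and delta-adjusted pattern-mixture models are announced as sensitivity analyses for MNAR.
- **Removal triggers (section 2.6, list of protocol violations).** They include "occurrence of severe AE, transfer to acute wards due to severe medical complications, futility of the intervention". Futility is defined by recovered upright tolerance plus thresholds on two mBI sub-items. Changes in listed drugs, missed sessions and withdrawal also count.
- **Expected pattern (Discussion).** The authors expect "lower occurrence of side effects (e.g., orthostatic hypotension) and related dropouts in the VEM arm". They also expect more futility stops in eDoC patients.
- **Schedule (Tables 1 and 3).** LCF, mBI and FDG-CCS are rated at T0, T1 and T2. Adverse events are recorded at every session.
- **Planned loss (Sample Size).** "To account for a possible dropout rate of 20%, a total of 118 patients will be enrolled (59 subjects per arm").

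**The concern.** A likelihood-based mixed model gives valid estimates when data are missing at random given what is in the model. It does not make the data so, and calling the assumption inherent hides what has to be argued. A patient lost before T1 and not seen at T2 has one LCF value, the baseline. The model then treats that patient's unseen T1 score as if it resembled the scores of retained patients with the same arm, centre and baseline.

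The triggers make that doubtful. Someone removed for a severe adverse event or a transfer probably has a worse T1 LCF than baseline predicts. Someone removed for recovery probably has a better one. If the mix of reasons is the same in both arms, the distortions largely cancel in the contrast. If it differs, they do not, and the Discussion expects a difference for side effects. At stake is the primary estimate: losing more poor-prognosis patients from TV than from VEM flatters TV and shrinks the apparent benefit of VEM.

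**Working it through.** **The plan's own figures.** The planned 49 per arm reproduces as the between-group test of a repeated-measures ANOVA with f = 0.248, m = 2 measurements and an assumed correlation of 0.5. The noncentrality is f²·N·m / (1 + (m − 1)ρ) = 0.248² × 98 × 2 / 1.5 = 8.04, which gives power 80.1% at N = 98. That calculation is not in dispute here. It supplies the scale of effect and of loss.

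**Inputs from the protocol**
- LCF in the source study: "an increase from 3.13 ± 1.41 to 3.60 ± 1.50 in the control group (n = 15") and "from 3.60 ± 1.05 to 4.40 ± 1.06 in the experimental group". The difference in gain is (4.40 − 3.60) − (3.60 − 3.13) = 0.80 − 0.47 = 0.33.
- Root-mean-square of the four SDs: √[(1.41² + 1.50² + 1.05² + 1.06²)/4] = 1.27, rounded to 1.3.
- Planned dropout of 20%: 0.20 × 59 = 11.8 patients per arm.

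**Inputs assumed, because the protocol gives none**
- T1 LCF is missing for every removed patient, with no T2 value. The ordinal model is approximated by linear ANCOVA on T1.
- Residual SD σ of T1 LCF given baseline: 1.0, or 1.3 × √(1 − 0.5²) = 1.126.
- Residual correlation r between each driver of removal and T1 LCF: 0, or 0.3 to 0.6 in size (negative for adverse events).
- Recovery removal 10% in both arms. Adverse-event removal 15% in TV and 5% in VEM. Total loss is then about 24% and 15%.

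**Formula.** If the worst fraction p on the adverse-event driver is removed, the mean residual of those retained rises by σ·r·φ(z)/(1 − p), where z is the upper-p normal quantile.
- TV, p = 0.15: φ(1.036)/0.85 = 0.2332/0.85 = 0.274
- VEM, p = 0.05: φ(1.645)/0.95 = 0.1031/0.95 = 0.109
- Bias in VEM minus TV ≈ −σ·r × (0.274 − 0.109) = −0.166·σ·r

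Equal recovery removal nearly cancels between the arms. A simulation with 600,000 patients per arm agrees:

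| σ | r (recovery / adverse event) | Formula: 0.33 + bias | Simulated |
|---|---|---|---|
| 1.0 | 0 / 0 | 0.33 | 0.33 |
| 1.0 | 0.3 / −0.3 | 0.28 | 0.28 |
| 1.0 | 0.6 / −0.5 | 0.25 | 0.25 |
| 1.126 | 0.3 / −0.3 | 0.27 | 0.27 |
| 1.126 | 0.6 / −0.5 | 0.24 | 0.24 |
| 1.126 | 0.6 / −0.6 | 0.22 | 0.22 |

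**Where the bias vanishes.** With 10% removal for each reason in both arms, the estimate is 0.33 at every correlation. It is also 0.33 whenever removal is unrelated to T1 LCF given arm and baseline. If T1 is rated after removal, nothing is missing.

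**Does the remedy work?** Regression imputation by arm, in the scenario of the table:
- Both drivers known without error: 0.33.
- Adverse-event driver only, without error: about 0.33.
- Adverse-event driver only, with measurement noise of equal variance: 0.26 to 0.30.

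Full recovery is partly built in, because removal was simulated from those same drivers. The noisy case is the more realistic guide.

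**The case against.** The other side has several good arguments.

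- **T1 may not be missing.** Violators are taken off treatment, not expressly off assessment, and stay in under intention-to-treat. This stands, and it is why the conclusion is conditional. But a 20% dropout allowance, transfers, withdrawals and a rule for the latest rating only matter if some later ratings are absent. If that rule means carrying baseline forward, it does not help: in the same scenario with σ = 1.126 the bias was −0.05 at r = 0.3 and −0.09 at r = 0.6.
- **T2 LCF is in the model.** A patient missed at T1 but seen at T2 contributes through the patient intercept. This stands and would soften the figures above.
- **MNAR analyses are planned.** They are, but as sensitivity analyses, so the primary estimate is unchanged.
- **Inherent is common shorthand, the formula is only an example, and auxiliary variables belong in the SAP.** The list of auxiliaries can indeed be left to the SAP. The point here is what the protocol does state: it presents MAR as coming with the model while listing removal rules that make it doubtful.

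A reader might infer more: that missing T1 LCF is not MAR and the contrast is biased. Neither follows. Omitting a predictor of removal breaks MAR only if that predictor relates to the unseen T1 LCF given the modelled data, and baseline LCF carries part of the pDoC/eDoC difference.

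A reader might also suppose that a working VEM sends more recovered patients out of its own arm. With recovery removal of 15% in VEM and 5% in TV, and adverse-event removal the other way round, the estimate falls to about 0.15 (σ = 1.0, r = 0.6 / −0.5). The Discussion expects futility stops to differ by diagnosis, not by arm, so that scenario is not supported.

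**Conclusion.** The point holds in conditional form. MAR given arm, baseline LCF and the random intercepts is an assumption that the protocol's own removal rules and expectations make doubtful, and the wording treats it as settled by the choice of model. If T1 LCF is missing after removal and only adverse-event removal differs by arm (15% against 5%), an effect of 0.33 becomes about 0.24 to 0.28, a loss of 15% to 27%. The most adverse pairing tried gives 0.22.

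The direction is towards zero in these scenarios. The size rests on assumed correlations, removal rates and residual SD, on a linear approximation, and on no T2 information. The documents do not establish that the bias will occur. The matter deserves a change before analysis but does not undermine the design.

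**What to change.** 1. State in section 2.6 that LCF is rated at the scheduled T1 and T2 for every randomised patient who can still be reached, whether or not treatment was stopped. This removes most of the problem at its source.
2. For LCF values still missing, replace the wording about an inherent MAR assumption with multiple imputation by arm. Use baseline LCF, diagnosis, centre, any T2 LCF, adverse-event count and grade, sessions delivered, and any mBI sub-items rated when futility is declared.
3. Use the post-randomisation variables in the imputation model only. Then fit the stated ordinal model to the imputed data.
4. Keep the delta-adjusted analysis as the MNAR sensitivity analysis, since recovery-driven removals can be only partly recovered under MAR.

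The cost is a few sentences, some programming, follow-up ratings for removed patients, and a slightly more complex primary analysis. The repair is partial. Adverse events are recorded at each session, but mBI and FDG-CCS are not scheduled between T0 and T1. At 5% to 15% of 59, each reason contributes only about 3 to 9 patients per arm, so the imputation will lean on its model.

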In the rehabilitation phase, the early recovery of the upright position (i.e., verticalization) is crucial to prevent secondary complications due to immobility (e.g., stasis pneumonias, deep vein thrombosis, pressure ulcers) [3], enable the stabilization of the hemodynamic balance [4], promote the cognitive performance improvement (especially vigilance and attention) [5], and to ameliorate the muscular-cutaneous trophism and the control of trunk and limbs. However, the Traditional Verticalization (TV) using a conventional tilt table can be hampered by orthostatic hypotension due to cardiac output reduction because of blood pooling in the lower extremities and/or co-existing central sympathetic system impairment [6]. Since its introduction by Czell in 2004 [7] the tilt table equipped with robotic-assisted lower limbs cyclic mobilization has been proposed as a safe and suitable device for a controlled verticalization to facilitate the adaptation to vertical posture in bedridden patients with brain-injury since the acute phase [8]. A combined assisted lower limbs mobilization can activate the musculo-venous pump that enhances counter gradient venous blood flow return to the right heart from systemic circulation, thus resulting in better cardiac output and lower side effects (e.g., orthostatic hypotension) occurrence [9,10]. However, despite the potential benefits and growing popularity of robot-based rehabilitation [11], no conclusive data on cognitive-motor effects of controlled verticalization in patients with sABI have been found, likely because of the methodological bias of the available clinical trials (e.g., small or heterogeneous cohorts ranging from acute to chronic patients, absence of clear randomization; lack of blinding in outcome assessors [5,8,12,13,14]. To minimize bias due to confounding, the present randomized controlled trial (VEM-sABI) will compare multiple clinical, neurophysiological, and biological effects of combined robot-assisted VErticalization and lower limbs Mobilization (VEM) versus a TV in a large cohort of patients with sABI admitted to multiple post-acute rehabilitation settings. The primary aim of the VEM-sABI study will be to evaluate the efficacy of VEM versus TV in promoting short-term recovery of cognitive functioning in a large cohort of patients with sABI. Secondary aims will be to evaluate VEM vs. TV in: (i) preventing or reducing spasticity; (ii) promoting lower limb movements; (iii) reducing functional disability; (iv) and an additional secondary aim will be to evaluate the usability and safety of the two devices from the professional’s point of view. Exploratory aims will be to evaluate the efficacy of VEM vs. TV in: (i) promoting the recovery of consciousness in patients with pDoC; (ii) preventing clinical complications; (iii) maintaining the possible improvement in clinical–functional measures at 1 month after treatment. Additionally, it is crucial to also investigate the patients’ physiological features (such as neurophysiological indices of brain activity and biomarkers of brain damage and plasticity) to accurately outline patients with higher probability to respond to the treatment and detect sub-clinical outcomes [15]. In this context, additional exploratory objectives of study will be to evaluate the effect of VEM vs. TV on brain functionality and neuronal plasticity.

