During each VEM or TV session, BP, heart rate (HR), and oxygen saturation will be monitored throughout the entire session to prevent complications associated with orthostatism (e.g., hypotension and syncope). In unconscious patients, these vital parameters will be continuously monitored. In conscious patients, they will be recorded at each verticalization step or whenever symptoms or clinical signs potentially indicative of hypotension or cardiac rhythm disturbances occur (e.g., reduced arousal, pallor, nausea). An ad hoc checklist (Adverse Events Report) will be used to record the following possible adverse events (AE), which will also be documented in REDCap: (i) orthostatic hypotension, defined as a sustained drop in systolic BP ≥ 20 mmHg or diastolic BP ≥ 10 mmHg within 3 min of tilt angle change, according to the diagnostic criteria established by the American and European Autonomic Societies [20]; (ii) postural tachycardia syndrome, defined as a sustained HR increase ≥ 30 bpm within 10 min of standing, in the absence of orthostatic hypotension [20]; (iii) bradycardia, defined as HR < 50 bpm; (iv) oxygen desaturation < 90%; (v) signs of excessive pain or clinical discomfort, particularly in patients with pDoC (e.g., agitation, self-removal of medical devices, violent or unsafe movements).

To ensure rapid activation of emergency procedures in the event of AE during verticalization, all patients must have a functioning intravenous access to allow prompt pharmacological intervention if needed. Airway suction, oxygen delivery systems, and a crash cart are readily available; physiotherapists are trained in their use. A nurse and a physician are available on the ward for rapid intervention if required. In the event of orthostatic hypotension, the following steps are implemented: (i) immediate return to the previous tilt angle; (ii) if unresolved, return to 0°; (iii) if hypotension persists, the patient is placed in the Trendelenburg position; (iv) if instability continues, pharmacological treatment is initiated under medical supervision via the pre-established IV access.

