In addition, we defined a graded framework for AE seriousness and relatedness to guide session management:-Mild AE: No session suspension required. Symptoms are transient and resolve without intervention (e.g., mild and temporary facial pallor without changes in vital signs);-Moderate AE: Interruption of a single session is required. Symptoms resolve within the same day (e.g., oxygen desaturation resolving after endotracheal suctioning);-Severe AE: Permanent discontinuation of treatment is considered in case of repeated or persistent AE unresponsive to intervention (e.g., hypotension not responding to reduction in tilt angle), or based on medical judgment prioritizing patient safety.

AEs will be managed according to the 90/385/EEC and 93/42/EEC regulations.

A concomitant usual care and rehabilitation interventions will continue without restriction for both arms. Regardless of allocation to the VEM or TV group, all patients will carry out the comprehensive rehabilitation program as designed by the participating center for the entire study period. The usual rehabilitation program consists of alternating bed positioning, passive limb mobilization, cognitive training, activities to facilitate recovery of consciousness (e.g., multisensorial stimulation), speech, and swallowing therapy. During VEM in sABI study, clinicians will be asked to exercise caution when prescribing “prohibited” (i.e., not permitted under the study protocol) and “proscribed” medications (i.e., permitted but requiring careful documentation and, when necessary, adjustment in timing or dosage). These medications may compromise safety (prohibited agents associated with orthostatic hypotension), and affect the interpretability of outcomes by influencing cognition, attention, arousal, or consciousness (proscribed medications) [21,22]. A list of contra-indicated medications and/or cautions is reported in the Appendix B. Information on pharmacological treatments will be collected at baseline and at all follow-up time points.

At the end of the fifth week of treatment (T1), and after 1 month from T1 (T2) a clinical–functional and neurophysiological evaluation will be performed. A serum blood sample will be collected at T2 (see Table 3).

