Age between 18 and 75 years; sABI due to traumatic, vascular, anoxic, or mixed etiology; Stable behavioral/cognitive diagnosis on at least 4 behavioral evaluations in 1 week using the Italian version of the CRS-R in patients with pDoC, or the LCF-based cognitive assessment in patients with eDoC; Time post-injury between 28 days and 6 months [1]; Not recovered upright station; Written informed consent by the patient’s legal representative/primary caregiver.	Severe medical conditions hampering verticalization (e.g., severe hypotension or conditions realizing hemodynamic instability, end stage or severe symptomatic heart failure with reduced ejection fraction, cardiac arrhythmia of new diagnosis or arrhythmic flare, severe hepatic failure, chronic severe lower limb arterio-venous disease, sepsis/septic shock, thrombus venous embolism of new diagnosis, severe autonomic dysreflexia); Severe medical conditions hampering lower limb mobilization (e.g., fractures, heterotopic ossifications); Severe medical conditions impacting EEG activity (e.g., sub-continuous or abundant EEG epileptiform abnormalities); Severe medical conditions influencing consciousness/cognitive status, such as severe hyponatremia or hypoglycemia; Contraindications to the use of Erigo^®^Basic and/or Erigo^®^Pro (Hocoma, Volketswil, Switzerland) as per technical data sheet (see Appendix A); Presence of prohibited drugs (see Appendix B).

Abbreviations: CRS-R = Coma Recovery Scale-Revised; eDoC = emergence from Disorder of Consciousness; EEG = electroencephalography; LCF = Level of Cognitive Functioning; pDoC = prolonged Disorder of Consciousness; sABI = severe Acquired Brain Injury.

**Table 3 jcm-14-06628-t003:** Summary of primary, secondary, and exploratory outcomes and measures.

Outcome	Timing, Measure
Primary outcome: Global cognitive functioning	At T0 and T1: LCF
Secondary outcomes:	
Functional disability Spasticity of lower limbs Muscular strength of lower limbs Functional independence Usability of devices from physiotherapists Adverse events	At T0, T1 and T2: DRS At T0, T1 and at T2: MAS At T0, T1 and T2: MRC. Additional clinical observation of spontaneous or reflex movement to pain stimulation in pDoC patients At T0, T1 and T2: mBI At T1: SUS Each daily session: AER
Exploratory outcomes:	

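### The adverse-event outcome and the interim safety analysis do not include transfers to acute wards, so a transfer not caused by a listed event shows only in exploratory analyses

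*Protocol article*

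**What the plan says.** Adverse events are a secondary outcome in Table 3, with the timing "Each daily session: AER". Section 2.3.2 describes the instrument: "An ad hoc checklist (Adverse Events Report) will be used to record the following possible adverse events (AE"), followed by five items: orthostatic hypotension, postural tachycardia, bradycardia, oxygen desaturation, and excessive pain or discomfort. The severity grades in the same section are framed by what happens to the session or the treatment. For the severe grade, "Permanent discontinuation of treatment is considered in case of repeated or persistent AE unresponsive to intervention", or on medical judgment. Neither transfer nor hospitalisation is named in the grades.

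Section 2.6 sets the scope of the interim look: "Interim analyses are planned at half of the expected sample for safety outcomes only (i.e., AEs"). The same section lists the protocol violations, among them "occurrence of severe AE, transfer to acute wards due to severe medical complications". The consequence of a violation is: "Patients violating the VEM-sABI protocol will be excluded from the VEM or TV treatment, but the last clinical observation will be considered".

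Complications also appear elsewhere. The Introduction gives "ii) preventing clinical complications" as an exploratory VEM-versus-TV aim. Table 3 measures it with the FDG-CCS at T0, T1 and T2. The Discussion announces an analysis of why patients drop out.

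**The concern.** Safety is one of the trial's stated purposes, and the Discussion describes this population as prone to clinical complications. Return to an acute ward is among the gravest events that the protocol itself foresees. Yet the safety outcome is a list of haemodynamic, respiratory and discomfort events around verticalization, and section 2.6 names transfer beside severe adverse events rather than among them.

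If transfers differ between arms and their causes are not on the list, neither the interim nor the final adverse-event comparison would show it. The trial could then report similar or better tolerability for one device while more of its patients went back to acute care. The exploratory analyses might pick this up, but only at the end and not as a safety result.

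**Working it through.** This is mainly a reading check, with a small calculation for scale.

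**1. Routes by which a transfer could reach an analysis**

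| Route | Where stated | Captures a transfer not caused by a listed event? |
|---|---|---|
| AER, secondary outcome | Section 2.3.2, Table 3 | Not as listed: five event types, transfer not among them |
| Severe adverse event grade | Section 2.3.2 | Only if the cause is recorded as an adverse event and graded severe |
| Interim analysis | Section 2.6 | No: limited to adverse events |
| FDG-CCS, exploratory | Section 2.4, Table 3 | Possibly, if rated at T1 or T2; outside the interim look |
| Dropout reasons | Discussion | Yes as a reason; purpose is to profile patients, not to compare safety by arm |

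**2. What happens to the FDG-CCS of a transferred patient**

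Table 1 schedules the scale at T0, T1 and T2, with none in weeks 1 to 5. For a patient transferred during treatment:
- If T1 or T2 is still rated, the complication can be scored.
- If both are missed and "the last clinical observation will be considered for statistical analysis" means carry-forward, the value used is the T0 score, from before the complication.
- If both are missed and the mixed-model wording of the same sentence governs, the patient contributes no post-baseline score.

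In the last two cases the event that ended treatment does not enter the score.

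**3. AER timing**

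Table 1 marks the AER in weeks 1 to 5 and again at T1 and T2. Table 3 gives daily sessions only. The two tables disagree on whether events after the last session belong to the outcome.

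**4. Scale, with assumed rates**

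Inputs from the article: 59 per arm, 118 in total, interim at half, so 118 / 2 = 59 patients. The transfer rate r is not given and is assumed. Expected transfers = r × n.

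| Assumed r | Interim, n = 59 | Final, n = 118 |
|---|---|---|
| 5% | 2.95, about 3 | 5.9, about 6 |
| 10% | 5.9, about 6 | 11.8, about 12 |
| 20% | 11.8, about 12 | 23.6, about 24 |

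The top row of the range is extreme: 0.20 × 118 = 23.6 equals the whole dropout allowance in the sample size section, and section 2.6 lists several other ways out of treatment.

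**5. Could a test on these counts settle anything?**

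Power of a two-sided 5% comparison of two proportions, normal approximation with pooled variance under the null, n per arm:

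Φ{[|p1 − p2| − 1.96 √(2p̄(1 − p̄)/n)] / √([p1(1 − p1) + p2(1 − p2)]/n)}

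- 5% versus 15%: n = 59 gives (0.10 − 0.1083)/0.0545 = −0.15, power 44%. At the interim (29.5 per arm) it is about 25%.
- 10% versus 20%: about 33% at the end and 19% at the interim.

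The counts would therefore serve as descriptive safety data by arm, not as a test.

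**The case against.** The strongest answer is that the article nowhere excludes transfers from adverse events. Listing two reasons for violation side by side does not make them mutually exclusive, and a transfer caused by a listed event is counted through that event. The severe grade leaves room for medical judgment. Adverse events are managed under named device directives and reviewed in monthly calls (section 2.5). The AER is also marked at T1 and T2 in Table 1, when no sessions take place, so it may not be purely a session form. Definitions of serious events may sit in the full protocol or an analysis plan, which are not at hand.

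Much of this stands, and it rules out three stronger readings that a reader might draw:

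- That transfers are handled only as violations, so that the gravest harm is absent from the results. The documents do not support this: complications are compared by arm through the FDG-CCS, dropout reasons are to be analysed, and the DRS, a secondary outcome, scores death as 30.
- That transferred patients will certainly be analysed as unchanged from T0. Section 2.6 removes violators from treatment, not from assessment. It refers to a mixed model under missing at random and plans sensitivity analyses for data missing not at random. Carry-forward of T0 is one reading, and it needs T1 and T2 to be missed.
- That a known number of patients will be lost from the safety tables, or that such complications arise mostly between sessions. The article gives no rate and no timing.

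What the answer does not do is bring transfers into the safety comparison. The directives and the monthly calls concern management and oversight, not an analysed outcome. The FDG-CCS is exploratory, rated at fixed visits and not part of the interim look. The scope of the safety outcome and of the interim analysis is stated in the article itself, so this is a rule stated too narrowly rather than a detail left for later.

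**Conclusion.** The point holds in limited form. As written, the adverse-event outcome and the interim safety analysis do not include transfers to acute wards for severe medical complications, unless the cause was itself recorded as an adverse event. Such transfers are otherwise reflected only in an exploratory scale, which may miss them if the patient is not rated at T1 or T2, and in the analysis of dropout reasons.

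The size is unknown. The figures of about 3 to 12 transfers at the interim and 6 to 24 at the end rest entirely on assumed rates of 5% to 20%, and they are upper bounds on what could go uncounted, since some transfers would follow a listed event. The conclusion also rests on reading the five-item checklist and the interim scope literally. A full protocol that already counts transfers as serious events by arm would resolve the point. It should be corrected, because it bears on a main claim of the trial and the change is small.

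**What to change.** - In Table 3 and section 2.6, add acute-ward transfer for a medical complication, and death, to the safety outcome. Count each per randomised patient, by arm, from T0 to T2, whether or not treatment has stopped.
- Include the same counts in the interim safety analysis as well as the final one, presented descriptively by arm.
- In the FDG-CCS analysis, do not carry the T0 score forward for transferred patients. Report the transfer as a complication event alongside the score.
- Reconcile the AER timing between Table 1 (weeks 1 to 5, T1 and T2) and Table 3 (daily sessions).

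The cost is wording and a little more tabulation. That removal reasons are collected is inferred from the dropout analysis in the Discussion. The sponsor should confirm it, and also that transfers and deaths after removal are recorded up to T2. The safety figures may look less favourable. No treatment, stopping or clinical management rule changes.
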